#### Additional mechanistic outcome measures

Cognition-related neural activity will be assessed with resting state fMRI and the following carefully selected fMRI tasks: (i) a spatial N-back working memory task and (ii) a novel grocery list strategic encoding paradigm. Alternate matched versions of the grocery list fMRI paradigm are used at the two testing times to minimize neural desensitization to the test stimuli. Structural MRI measures of interest are hippocampal and cortical volume, cortical thickness, and white matter integrity. The PET measure of interest is hippocampal and prefrontal cortex SV2A [^11^C]UCB-J binding as a readout of presynaptic density, as stated in the aims.

To further increase insight into the underlying neurobiological mechanisms involved in the potential beneficial cognitive effects of hypoxia cognition training, blood samples from first day (day 1) and second to last day of treatment (day 19) will be analyzed for the exploratory purpose of investigating whether baseline levels and/or changes of peripheral biomarkers, including EPO, are correlated with cognitive improvement.

Blood based biomarkers of neuroplasticity (e.g., brain derived neurotrophic factor), inflammation (e.g., interleukin factors), and EPO will be obtained at baseline (BL) and end of treatment for explorative analyses.

#### Biochemistry

Blood test data is pseudo-anonymized by the Clinical Biochemistry Department—Section for External Projects, Copenhagen University Hospital. This is done by producing serial numbers that are attached to the individual blood tests and a separate electronic conversion key linking the serial numbers to participants ID numbers. Research blood samples will be transferred to the Neuropsychiatric Laboratory, Frederiksberg Hospital, and stored at − 80 °C until use. The collected blood samples will be stored until they are analyzed in a research biobank set up for this project. Measurements will be performed at Department of Clinical Pharmacology, Rigshospitalet. The research biobank will cease at the end of the project (expected date 01 January 2029), and any excess material will then be transferred to Cimbi Biobanken, which is an existing and approved biobank for future research under the Neurobiological Research Unit, Copenhagen University Hospital, Rigshospitalet.

### Statistical analyses

#### Primary, secondary, tertiary, and exploratory outcome measure analyses

Behavioral data from neuropsychological test score performance, subjective cognitive impairments, quality of life, level of functioning, psychosocial functioning, and mood symptoms (i.e., data from the primary, secondary, and tertiary outcomes) will be analyzed using mixed model design. Hence, the analyses investigate how the mean score of each outcome changes over time in each treatment group and testes for interaction effects (i.e., are the trajectories different between the groups). All analyses will be based on an intention-to-treat (ITT) principle. Hence, all participants will be analyzed based on their allocated intervention arm. Participants with incomplete data will also be included in the analyses without any ad hoc imputation [71]. No interim analyses will be performed. A nonblinded researcher will pseudo-anonymize the data prior to analysis, and data analyses will thus be conducted by blinded researchers.

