**Fig. 1 Fig1:**
[figure not shown]
Overview of events across parallel sub-studies

Sub-study 1 involves four intervention groups: (1) normobaric hypoxia (12% O_2_) combined with cognitive training, (2) hypoxia (12% O_2_) with no training, (3) cognitive training under normoxia (20% O_2_), and (4) normoxia (20%) with no training in a double-blinded controlled design. This design enables us to disentangle combined and separate effects of altitude-like hypoxia and cognitive training. Participants are randomized in blocks and undergo interventions in these groups for practical reasons. During the three-week treatment, participants breathe 12% ambient oxygen (≈ 4400 m altitude) or approximately normal sea-level oxygen (20%) in a treatment room, 3.5 h daily, six days per week (18 sessions in total). After a blood test (days 1, 6, 20) and light standardized breakfast, they enter the treatment room. Here, they sit at a desk separated by desk dividers. On iPads, they perform cognitive training or matched control games without cognitive benefits. Cognitive training is interleaved by short breaks, during which the participants can relax or walk on a treadmill inside the room. This is to avoid complete physical inactivity throughout the 3.5 h sessions and thereby make the sessions more pleasant for participants. Participants undergo cognition assessments in weeks 1 (baseline), 4, and 8 and functional and structural MRI in weeks 1 and 8, when red blood cell counts are comparable between groups. Participants in the two extreme groups (normobaric hypoxia with cognitive training and normoxia with no training) will also undergo PET scanning in week 4 (post-treatment). Participants will be recruited consecutively for the PET scans until an equal distribution in each of the extreme intervention arms (i.e., hypoxia with cognitive training and normoxia with no training), sex, and age group is achieved.

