### Randomization and blinding

Randomization is conducted in the database program REDCap [51], which is also used to store the collected data, utilizing a 1:1 allocation ratio. Randomization occurs after inclusion of the participants planned to undergo treatment sessions together. Treatment groups are stratified for age (> 27 in sub-study 1 of generally young volunteers/ > 35 in sub-study 2 of patients). For randomization purposes, date of birth is registered to determine the stratum to which the participant belongs at the time of enrolment. Study identification numbers are given consecutively within each stratum and treatment arm. Randomization is conducted in the randomization module in REDCap, where an un-blinded researcher inputs the stratum and the program then retrieves the allocated intervention. To ensure blinding of the outcome-assessors, the randomization module in REDCap is only accessible to the researchers, who are not involved in evaluation of the efficacy parameters.

Healthy participants in sub-study 1 are blind to the oxygen condition since the low/normal oxygen air blown into the room is of equal temperature and humidity. Furthermore, they are told that they receive one of two forms of cognitive training, which effectively blinded participants in a previous study [52]. After study completion, we will assess whether blinding has been maintained for each participant, since there is a small risk that some participants develop symptoms of mild altitude sickness which could unblind them to their intervention. Blinding of the outcome assessors is ensured by their absence during the training visits (where oxygen levels are displayed and monitored on a screen outside the room). Participants will be instructed not to disclose any information concerning their intervention during outcome assessments and under no circumstances will the allocation be revealed to the outcome assessors. The training visits are conducted by researchers who are not involved in outcome assessments.

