#### Primary outcome measure

The primary outcome measure is changes in a cognitive composite score, consisting of neuropsychological tests covering attention, memory, and executive functions from baseline to week 4. We have previously demonstrated an improvement on this *speed of complex cognitive processing* composite measure in patients with BD after 8 weeks of EPO treatment [28]. In the present trial, the specific tests included in the primary composite outcome measure are the Rey Auditory Verbal Learning Test (RAVLT) [55], The Repeatable Battery for the Assessment of Neuropsychological Status (RBANS) Coding [56], Verbal Fluency with the letter “D” [57], Wechsler Adult Intelligence Scale (WAIS)-III Letter-Number Sequencing [58], Trail Making Test Part B (TMT-B) [59], and Rapid Visual Information Processing (RVP) from the Cambridge Neuropsychological Test Automated Battery (CANTAB, Cambridge Cognition Ltd.). To derive the cognitive composite score, we will z-transform and sum performance scores from RAVLT total recall, TMT-B, WAIS-III Letter-Number Sequencing, RBANS Coding, Verbal Fluency (letter “D”), and RVP speed for correct responses [28].

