#### MRI analyses

Whole-brain and hippocampal volume and cortical thickness will be accessed using the FMRIB Software Library (FSL) vertex-based analysis and FreeSurfer Image Analysis Suite, respectively. White matter integrity is assessed with tract-based spatial statistics.

Resting state and task-based functional MRI (fMRI) data will be preprocessed and analyzed with the FMRIB Expert Analysis Tool (FEAT; latest version available at trial completion) part of FMRIB’s Software Library (FSL; www.fmrib.ox.ac.uk/fsl). For resting-state fMRI data, we will use Multivariate Exploratory Linear Optimized Decomposition into Independent Components (MELODIC) to conduct group-level ICA by multi-session temporal concatenation, identifying the common resting state networks across the groups. Furthermore, fMRI data from the N-back working memory task and the grocery list encoding and retrieval tasks will be analyzed using a region-of-interest analysis to assess differences between the intervention and control groups in neural activity in the dorsal PFC (dPFC) after completing 4 weeks of treatment (adjusting for any difference in neural activity at baseline). We will also conduct volume-of-interest analyses of the dPFC for the N-back task and for both the dPFC and hippocampi for the word encoding task to investigate our hypotheses. Finally, exploratory whole-brain analyses will be conducted to investigate any treatment-related effects in other brain regions.

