### Sample size and power calculation

Power calculations were performed with the software program G*Power 3.1.9.4 [74] and were based on the primary hypothesis that altitude-like hypoxia combined with cognitive training produces robust sustained cognitive improvement compared with normoxia and no training (hypothesis i). As hypoxia triggers the endogenous production of EPO, we based the power calculation on our previous clinical study of subcutaneous EPO treatment in which we demonstrated clinically relevant cognitive enhancement [75]. In that study, the differential change between EPO and placebo groups in the same cognitive composite score as we apply in the present study was 0.5 standard deviations (SD) [75]. Assuming an effect of 0.4 SD differential change (medium effect size) between the two groups and 0.5 SD of the change, we will achieve > 80% power to detect an effect at an alpha level of 0.05 by including 26 participants per group. This number of participants provides adequate power for the structural and functional MRI investigations based on our previous studies of EPO [30, 32, 33]. To accommodate for up to a 20% drop-out, we will include 30 participants per treatment arm; i.e., 120 participants in sub-study 1 and 60 patients in sub-study 2.

For PET imaging of SV2A [^11^C]UCB-J binding (reflecting presynaptic density), power calculations involved the following assumptions: (i) the average (SD) *BP*_ND_ in the frontal cortex in healthy participants is 3.36 (0.38) (based on in-house data), and (ii) the combined intervention will lead to a 10% increase in *BP*_ND_. With these assumptions, we will achieve a power of 0.82 to detect an effect at significance level of 0.05 post-treatment of the combined intervention (primary aim) with *n* = 20 per treatment arm using a two-tailed, independent-sample *t*-test.

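### As described, the primary mixed model amounts to an unadjusted change-score comparison without the age stratum; a common baseline mean plus age stratum by visit would gain a little power at no cost

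*Protocol article*

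**What the plan says.** The section on primary, secondary, tertiary and exploratory outcome analyses says of the mixed model that "the analyses investigate how the mean score of each outcome changes over time in each treatment group", and that it tests for "interaction effects (i.e., are the trajectories different between the groups". It names no covariates and excludes none. Analysis is by intention to treat, and incomplete participants are kept without imputation.

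The section on the primary outcome measure defines the endpoint as a change: "The primary outcome measure is changes in a cognitive composite score", from baseline to week 4. The sample size section powers on change as well: "Assuming an effect of 0.4 SD differential change (medium effect size) between the two groups and 0.5 SD of the change". It arrives at 26 per group, raised to 30 to allow for up to 20% drop-out.

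The section on randomisation and blinding says: "Treatment groups are stratified for age (> 27 in sub-study 1 of generally young volunteers/ > 35 in sub-study 2 of patients". Allocation uses a fixed ratio ("utilizing a 1:1 allocation ratio"). No analysis section mentions the age stratum.

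The MRI section, by contrast, does state an adjustment for its region-of-interest comparison: "adjusting for any difference in neural activity at baseline".

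**The concern.** Taken together, the endpoint, the model and the power calculation describe a difference in mean change with no baseline covariate. In a randomised trial the arms share one baseline mean in expectation. A model that uses this fact, or that conditions on the baseline score, is at least as precise in all but very small samples, and it removes the chance baseline difference that a change score corrects only in part. The authors state such an adjustment for an imaging outcome but not for the primary one.

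Age was thought important enough to stratify on. If age predicts how much participants improve, a model without it gives up precision that the stratification was meant to secure.

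What is at stake is power, in a trial with little to spare: 26 per group is the smallest number that reaches 80%, and the plan's own drop-out allowance leaves fewer than that.

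**Working it through.** **Inputs.** From the sample size section: difference 0.4, SD of change 0.5, alpha 0.05, 26 per group, 30 recruited, up to 20% drop-out. Assumptions: the test is two-sided (sidedness is not stated for the primary outcome), and the composite has SD 1 at both visits.

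**1. The plan's own figure.** Standardised difference d = 0.4 / 0.5 = 0.8. A two-sample t-test (noncentral t) gives power 0.7915 at 25 per group and 0.8075 at 26. The stated 26 reproduces and is the minimum. After 20% drop-out, 30 × 0.8 = 24 remain, and power is 0.774.

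**2. What the described model estimates.** With a free mean for each arm at each visit, unstructured covariance and complete data, the week-4 group-by-time contrast equals the difference in mean change scores.

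**3. Implied correlation.** Var(change) = 2(1 − r) = 0.5² = 0.25, so r = 0.875.

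**4. Baseline adjustment.** Residual variance = 1 − r² = 1 − 0.7656 = 0.2344, so the SD is 0.484. Ratio to the change-score variance: 0.2344 / 0.25 = 0.9375, which is (1 + r)/2. In 20,000 simulated trials with 26 per group the ratio was 0.952, slightly higher because the slope is estimated. The saving is therefore about 5 to 6%.

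| Per group | Change score | Baseline-adjusted (1 df lost) |
|---|---|---|
| 26 | 0.81 | 0.83 |
| 24 | 0.77 | 0.80 |

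The number needed for 80% power falls from 26 to 25 per group.

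**5. Sensitivity to r.** Keep the SD of change at 0.5 and vary r. The composite SD is then 0.5/√(2(1 − r)) rather than 1; for example, r = 0.7 implies 0.5/√0.6 = 0.65. Power at 26 per group is 0.904 for r = 0.5, 0.885 for 0.6, 0.866 for 0.7, 0.846 for 0.8 and 0.827 for 0.9.

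**6. Age stratum.** A term that is constant over a participant's visits drops out of within-person differences. In the free-baseline model an age main effect therefore leaves the week-4 contrast unchanged. A generalised least squares check (three visits, 30 per arm, complete data, age acting on level) gave an estimate of 0.6687 and a standard error of 0.1291 both with and without it. Only age by visit can matter there, and only if age predicts change. The document gives no figure for that. Purely as an illustration, suppose the stratum explained 2%, 5% or 10% of the remaining variance on top of baseline adjustment at r = 0.875. Power would be 0.839, 0.850 or 0.868 at 26 per group, and 0.807, 0.819 or 0.839 at 24.

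**The case against.** The strongest reply is that this is a condensed article. It is silent on covariates rather than excluding them, and the analysis plan may already set a common baseline mean, which its wording would also allow. That stands: a reader might infer that the authors decided against adjustment, and the text does not show this. The point is about the model as described, which, read with the change endpoint and the change-score power calculation, is unadjusted.

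It is also fair that baseline is not discarded, since it enters as a repeated measure. With r = 0.875, a change score differs from a baseline-adjusted estimate by 0.125 of the chance imbalance. At 30 per arm, one standard error of imbalance is √(2/30) = 0.26 SD, so the leftover is about 0.03 SD against a target of 0.4 SD. It is random error, not bias.

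Two stronger readings are tempting and are not supported:

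- **Standard errors too large for the stratified design.** For this contrast that depends on age predicting change, for which the document gives no information.
- **A PET t-test that needs replacing.** PET recruitment aims at balance ("Participants will be recruited consecutively for the PET scans until an equal distribution in each of the extreme intervention arms", sex and age group). But the t-test appears only in the power calculation, and the PET analysis section names no group test. The balancing is a recruitment quota, not a randomisation stratum.

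**Conclusion.** The point holds as a modest loss of precision. The described primary analysis is valid and unbiased, and 26 per group is correct for it. A better method is available from data the trial collects anyway.

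The baseline gain is about 6% of variance, two power points at 26 per group, or one participant per group. Its practical use is at the plan's own worst-case drop-out, where it brings power from 0.77 back to the 80% target, but only just. These figures rest on SD 1 at both visits and a two-sided test; a lower correlation with the same SD of change would make the gain larger. The gain from age depends on how far age predicts change and cannot be sized from the document.

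**What to change.** State in the analysis plan, for both sub-studies, that the primary mixed model:

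- constrains the arms to a common baseline mean (constrained longitudinal model) or, equivalently in purpose, models the post-baseline visits with baseline score by visit as a covariate; and
- includes age stratum, as used in randomisation, and age stratum by visit. The main effect alone is not enough if baseline means are left free.

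The reported effect remains the week-4 difference between arms. The baseline composite and the age stratum are already recorded, so the cost is wording and a few degrees of freedom. No interim analyses are planned, and recruitment was still open at the article's date (April 2024, with completion planned for June 2025). The specification should be dated and fixed before the allocation is unblinded for analysis. If the analysis plan already contains these terms, a sentence confirming it settles the point.

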Sub-study 2 involves two intervention groups: (1) normobaric hypoxia (12%) combined with cognitive training 3.5 h daily, five to six days per week for three weeks (16 sessions in total), and (2) treatment as usual (TAU) in an assessor-blind controlled design. Patients in the TAU group will initially be assessed at the same time points as the active group with neurocognitive testing at baseline, week 4, and week 8, fMRI at baseline and week 8, and PET in week 4. After completed testing at week 8, patients in the TAU group undergo the three-week active intervention, followed by one additional neurocognitive assessment and mood rating in the week after treatment completion. The inclusion of this TAU arm rather than an active control group was chosen to ensure patient motivation and minimize attrition in this time-intensive study. Similar study designs with TAU control groups are common in pro-cognitive intervention studies investigating novel treatments in mood disorders and schizophrenia [39, 40]. Although patients will not be blinded to their allocated treatment arm, neurocognitive test results are generally not susceptible to placebo effects [41, 42] and assessments will be carried out by blinded, fully trained research assistants (psychology students).

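### The stated primary analysis tests whether trajectories differ between groups, but the primary outcome and the sample size rest on one two-arm comparison of change at week 4

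*Protocol article*

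**What the plan says.** Three parts of the Protocol article bear on the primary test.

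- **Primary outcome measure.** The outcome is change in a composite of tests "covering attention, memory, and executive functions from baseline to week 4". This fixes the endpoint and the visit.
- **Sample size and power calculation.** The calculation is "based on the primary hypothesis that altitude-like hypoxia combined with cognitive training produces robust sustained cognitive improvement compared with normoxia and no training". This fixes two arms. The inputs are a difference of 0.4, an SD of change of 0.5, alpha 0.05 and 26 per group.
- **Primary, secondary, tertiary, and exploratory outcome measure analyses.** One sentence covers the behavioural measures at every level: "data from the primary, secondary, and tertiary outcomes) will be analyzed using mixed model design". The next sentence says that the analysis "testes for interaction effects (i.e., are the trajectories different between the groups".

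The design is described under Study design and procedure: "Sub-study 1 involves four intervention groups" and "Sub-study 2 involves two intervention groups". For sub-study 1, "Participants undergo cognition assessments in weeks 1 (baseline), 4, and 8"; sub-study 2 tests cognition on a matching schedule. No section names the week-4 difference between the combined arm and a stated comparator as the test that decides the primary hypothesis.

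**The concern.** A test of whether trajectories differ is not the same question as whether one arm beats another at one visit. Taken as written in sub-study 1, it pools four arms and two post-baseline visits. Two of those arms, hypoxia alone and training alone, are not part of hypothesis (i), yet hypothesis (iii) expects both to show some effect. Week 8 is not part of the primary outcome.

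A significant interaction could therefore be reported as support for hypoxia plus training when it came from another arm or from week 8. The quoted power also belongs to a different test from the one described. Finally, the text leaves the analyst free to choose afterwards among the interaction, the week-4 contrast, the week-8 contrast and several pairwise comparisons.

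**Working it through.** **Step 1: reproduce the plan's figure.** Two-sample t-test on change scores, difference 0.4, SD 0.5, 26 per arm. The sidedness is not stated; two-sided 0.05 is assumed.

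- Standardised difference: 0.4 / 0.5 = 0.8.
- Noncentrality: 0.8 × √(26/2) = 2.884; critical t on 50 df: 2.009.
- Power: 0.807 (one-sided: 0.885).

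The stated power above 80% reproduces as a single two-arm contrast.

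**Step 2: degrees of freedom of the stated test.** For a group-by-time interaction with categorical visits, df = (arms − 1) × (visits − 1).

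- Sub-study 1: (4 − 1) × (3 − 1) = 6.
- Sub-study 2: (2 − 1) × (3 − 1) = 2.

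**Step 3: when the interaction rejects.** Work with the vector of changes at weeks 4 and 8, SD 0.5 at both and correlation r between them. The documents do not give r, so 0.3 to 0.7 is assumed. The noncentrality is λ = n Σ (μ − μ̄)′ S⁻¹ (μ − μ̄), summed over arms, with n = 26. If one arm of four differs by 0.4:

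- at both visits: λ = 26 × (3/4) × (0.16/0.25) × 2/(1 + r) = 12.48 × 2/(1 + r), which is 16.64 at r = 0.5;
- at one visit only: λ = 12.48/(1 − r²), which is 13.71 at r = 0.3 and 24.47 at r = 0.7.

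Rejection probabilities come from the noncentral F. The ranges span r = 0.3 to 0.7 and two conventions for the denominator df: arms × (n − 1), and twice that.

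| True effect (week 4 / week 8), arms not named at 0 | Interaction significant | Week-4 contrast significant |
|---|---|---|
| Sub-study 1: training alone 0.4 / 0.4 | 0.81–0.92 | 0.05 |
| Sub-study 1: training alone 0.4 / 0 | 0.77–0.97 | 0.05 |
| Sub-study 1: combined arm 0 / 0.4 | 0.77–0.97 | 0.05 |
| Sub-study 1: combined 0.4 / 0.4 | 0.81–0.92 | 0.81 |
| Sub-study 1: combined 0.4 / 0.4, each single arm 0.2 / 0 | 0.86–0.90 | 0.81 |
| Sub-study 1: combined 0.4 / 0.4, each single arm 0.2 / 0.2 | 0.60–0.76 | 0.81 |
| Sub-study 2: combined 0.4 / 0.4 | 0.78–0.89 | 0.81 |
| Sub-study 2: combined 0 / 0.4 | 0.75–0.96 | 0.05 |

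In the first three rows the interaction is usually significant although the primary contrast is null. By the F-test's symmetry, the training-alone rows apply equally to hypoxia alone. Rows four to six show that power can lie above or below 0.81.

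**The case against.** The strongest reply is that the article never calls the test an omnibus one, gives no degrees of freedom, and does not say that a joint test decides the primary hypothesis. In a mixed model with categorical visits, the group-by-week-4 coefficient is exactly the difference in change to week 4. The outcome section supplies the visit and the sample size section the two arms, so the sections can be read as compatible with the right contrast, with the details left to an analysis plan that is not shown. This stands in part: the 6-df test is an inference from the wording, and the right estimate is available from the same model. It does not remove the point. The article chose to state the test and explained it in parentheses as a comparison of trajectories. It is more specific elsewhere: the task fMRI analysis compares intervention with control adjusted for baseline, and the PET power calculation names a t-test. A later plan would have to replace the sentence, not just add to it.

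Four stronger readings are tempting and are not supported.

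- **That a significant result may say nothing about hypoxia plus training in either trial.** Sub-study 2 has only that arm and treatment as usual, so any interaction there concerns the combined treatment.
- **That the stated test is underpowered.** Under the plan's own expectations, a sustained combined effect and transient single-arm effects (taken here as 0.2 at week 4 only), the interaction has power 0.86 to 0.90, above the contrast's 0.81. The lower figures need single-arm effects that persist, or a combined effect that fades.
- **That the analysis discards the factorial structure.** The article says of the four arms: "This design enables us to disentangle combined and separate effects of altitude-like hypoxia and cognitive training". A four-group model with visits is a recoding of hypoxia by training by visit, so those effects remain estimable.
- **That week 8 must be the first secondary outcome.** That is a preference about hierarchy.

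It is also fair that a component working alone but not in combination is the reverse of what the investigators expect, and that they will see the arm means. Those rows show what the test can respond to, not what is likely.

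**Conclusion.** The point holds as a mismatch between the stated test and the endpoint and contrast that define and power the primary hypothesis. It applies in full to sub-study 1. There the plain reading is a 6-df interaction that is significant with probability about 0.8 to 0.97 when a 0.4 effect lies only in a single-modality arm or only at week 8, so it does not by itself test hypothesis (i). In sub-study 2 the open question is only whether week 4, or weeks 4 and 8 jointly, decides.

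The issue is the meaning of a significant result. A reader might infer a flawed sample size or a general loss of power. The documents do not support either from this point: the sample size fits the week-4 contrast, and the interaction may have more or less power than that contrast.

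The size rests on 26 per arm, an SD of change of 0.5 at both visits, a two-sided 0.05 level, an assumed correlation of 0.3 to 0.7 and assumed single-arm effects. The conclusion that the interaction can reject with the primary contrast null does not depend on the exact values. It is an inexpensive clarification that should be made before the data are analysed, not a defect that undermines the trial.

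**What to change.** State one primary test per sub-study: the single-degree-of-freedom contrast, estimated from the planned mixed model, of change in the composite between baseline and week 4. The comparison is hypoxia plus training against normoxia without training in sub-study 1, and against treatment as usual in sub-study 2.

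Report as secondary or supportive the overall group-by-time interaction, the same contrast at week 8 (which bears on whether the effect is sustained), and, in sub-study 1, the hypoxia, training and hypoxia-by-training contrasts.

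The cost is a change of wording. The data, model and sample size stay the same, and the quoted power then belongs to the named test. The one thing given up is the overall interaction as a route to a positive primary result. The article plans no interim analyses, so the wording can be settled before results are seen, provided this is done before the analysis begins.
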